## Background on the intervention

Contingency management (CM), a behavior change strategy that reinforces positive health behaviors with incentives (e.g., cash), has been used in clinical trials to reduce tobacco and substance use in the general population.^21-24^ Smokers who abstain receive modest incentives; these incentives reinforce the healthy behavior.^21^ There have been clinical trials that have incorporated CM for the treatment of tobacco dependence among low-income pregnant women and persons with mental health or substance use disorders.^23,25-29^ Recent research, including uncontrolled pilot studies ^30,31^ and two recent pilot RCT,^32,33^ has demonstrated the feasibility of short-term CM (8 weeks or less) for smoking cessation among homeless adults. Some evidence suggests that extended CM, defined as CM for ≥12 weeks, can be efficacious in promoting long-term abstinence for ≥6 months.^21,34-39^ There are no feasibility trials evaluating extended CM to promote long-term abstinence among homeless adults, and none that have been adapted to safety net health clinics.

In this pilot randomized controlled trial (RCT), we will (1) adapt a known-efficacious extended CM cessation intervention to a novel population and setting, with the ultimate goal of increasing long-term abstinence among homeless adults seeking care in safety net health clinics, (2) develop a corresponding RCT protocol, and (3) conduct a pilot RCT to assess the feasibility and acceptability of the RCT. If the pilot RCT is feasible and acceptable, we will test the adapted intervention in a subsequently-funded, full-scale randomized controlled trial.

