**Abstinence assessment schedule*.*** All other aspects of the study protocol will be identical across the two experimental groups. Participants will be asked to choose a quit date within 7 days of providing consent,^26,30,32,33,100^ and will meet study staff at TWUHC or ZSFG on the day of the quit attempt (Table 1). Participants will meet daily for the first 7 days (week 1), twice weekly for the next 3 weeks (1 month), once weekly for the next 9 weeks (3 months), and monthly until the one-year follow-up (1 year). Assessment visit schedule is identical for both groups. At each of the scheduled assessment visits, participants will provide a CO sample and complete a short questionnaire on cigarette consumption, quit attempts since the last visit, the length of the last quit attempt, and use of medications and services. Questionnaires will be built on REDCap, and administered by study staff using an iPad.

***Abstinence assessment.*** As in prior studies, ^26,30,32,33,100^to determine eligibility for CM, we will assess point-prevalence abstinence with CO monitoring, using a cut-off of CO≤ 5 parts per million (ppm).^98^ For primary outcome assessment, we will confirm abstinence among participants who self-report abstinence and meet criteria for abstinence based on CO with urinary anatabine and anabasine (i.e. metabolites of tobacco) using a cut-off of <2 ng/ml ^101^ (analyzed by the UCSF Cancer Center Tobacco Biomarkers Core ^102^). Urinary anatabine and anabasine are tobacco alkaloids that are useful as confirmatory biomarkers to verify abstinence among patients who are using NRT for smoking cessation, and for whom urinary cotinine would not be appropriate.^101^

**Data collection reimbursements*.*** We will reimburse all participants with $20 for completing the baseline questionnaire, $15 each for questionnaires at 2, weeks, 1 month, and 3 months, and $25 each for questionnaires at 6 months and 1-year follow-up. Between 6 and 12 months, all participants will receive $5 for checking in at each monthly visit and providing a CO specimen. The total amount that all participants could earn for 1 year of participation exclusive of CM is $145 and as much as $620 inclusive of CM ($145+$475).

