## Adherence Assessment

Using a combination of qualitative and quantitative methods, we will evaluate whether: 1) we met our screening and recruitment goals, 2) the randomization scheme worked and that participants were willing to be randomized, 3) the CM intervention was delivered with fidelity, 4) the retention procedures enabled tracking and retention, 5) the outcome assessments were valid, reliable, and complete, and 6) participants adhered to the protocol (Table 2).

| **Table 2: Feasibility and acceptability outcomes** | | |
| --- | --- | --- |
| Outcomes | **Measure** | **Threshold** |
| Screening | # opting out, # screened | 40 screened per month |
| Recruitment | # enrolled per month | 8/month for 12 months |
| Randomization | Proportion enrolled who are randomized | 90% randomized to intervention and control arms^32^ |
| Fidelity | Observations of incentive payment delivery | Incentive payments that are due are delivered within 2 days of the visit by study staff |
| Adherence | Protocol adherence to the CO assessment schedule  Attendance to counseling sessions  Adherence to NRT among those prescribed NRT | 75% of those enrolled will provide a CO sample at 60%-70%, i.e., 14 -17 out of 25 possible assessment visits^32,33^  75% will attend at least 6 out of 12 counseling sessions during the treatment duration^33^  75% will adhere to using NRT for at least half of the treatment duration^33^ |
| Retention | Proportion of the sample retained as a result of retention procedures | 2 weeks (85%), 3-month (85%), 6-month (75%), and 1 year (75%) retention rates |
| Assessment | Proportion who completed all questionnaires | 75% completed all questionnaires |
| Acceptability | Questionnaire and qualitative interviews with staff and patients | 75% satisfied with the overall intervention |

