## Schedule of Activities

| **Assessments/Procedures** | **Screening** |  |  | **Study Intervention Period** |  | **End of Study Intervention** | **Follow-up** |
| --- | --- | --- | --- | --- | --- | --- | --- |
| **Study Visit / Day**  **(Window, # Days)** | **Visit -1/enrollment** | **Visits 2-8 / Week 1**  **Daily assessment** | **Visit 9-14 / Weeks 2- 4**  **Bi-weekly assessment** | **Visits 15-22/Weeks 5-13**  **Weekly assessment** | **Visits 23-25/Weeks 16-24**  **Monthly assessment** | **Visit 27 / Week 52**  **1 year follow-up** |  |
| Informed Consent^[[1]](#footnote-2)^ | **X** |  |  |  |  |  |  |
| Inclusion/Exclusion Criteria | **X** |  |  |  |  |  |  |
| Medical Record Review | **X** | **X** | **X** | **X** | **X** | **X** | **X** |
| Concomitant Medications | **X** | **X** | **X** | **X** | **X** | **X** |  |
| Adverse Events | **X** | **X** | **X** | **X** | **X** | **X** | **X** |
| Randomization/Assignment to Intervention | **X** |  |  |  |  |  |  |
| Administration of Study Intervention |  | **X** | **X** | **X** | **X** |  |  |
| Protocol-Specific Assessments/Procedures^2^ | **X** | **X** | **X** | **X** | **X** | **X^3^** | **X** |

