## Statistical Analysis Plans

1. ***Statistical analyses****.* Because pilot studies are too small to definitively test hypotheses or estimate precise effect sizes, we do not propose any inferential statistics. Primary analyses will include descriptive statistics of the feasibility and acceptability indicators, comparing each statistic (e.g., % retained) to its tabled threshold (above, see Section 5.2). Above-threshold findings will suggest a reasonable level of feasibility and acceptability for the corresponding aspects of study procedures. Any sub-threshold finding would suggest that remedial modifications to study procedures and/or design would be required prior to moving forward with a full-scale RCT. We also will examine descriptive statistics of the primary and secondary clinical outcomes and include exploratory analyses of relevant biological variables such as age, sex, and race/ethnicity. To the extent possible, descriptive anaylses will consider whether feasibility and acceptability outcomes were consistent across service providers and service settings.

.

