
# 2.  Description of Adverse Event Grading and Anticipated Adverse Events

In this study, we do not anticipate moderate or severe adverse events (AE).  AE will be scored as follows:

1. = No adverse event or within normal limits
2. = Mild AE – not requiring follow-up
3. = Moderate AE – resolved with follow-up
4. = Severe AE – resulted in inability to carry on normal activities and required professional medical attention, requiring hospitalization
5. = Life-threatening or disabling AE – results in an immediate risk of death and/or results in persistent or significant disability
6. = Fatal AE

We anticipate at most mild AE, including potential adverse effects of nicotine withdrawal or hunger among those reducing consumption or quitting cigarette smoking. Risks of participating in one-on-one counseling sessions and assessment interviews include fatigue from answering questions, worry about loss of confidentiality/privacy, and perception of coercion to participate. The Principal Investigator (PI), [name], in consultation with the research team, is responsible for evaluating each AE and for determining whether the AE affects the risk/benefit ratio of the study and whether modifications to the protocol and consent form are required.

Participants will attend abstinence assessment visits according to the following schedule: daily visits for the 1^st^week, twice weekly for the next 3 weeks (1 month), once weekly for the next 8 weeks (3 months), and monthly until the one-year follow-up (1 year). In addition, participants will be required to attend cessation services at the TWUHC that include behavioral counseling and pharmacotherapy. At each visit, we will ask participants whether they had experienced any adverse effects since the last visit. Participants will also be encouraged to call the study team in between visits if they were to occur.  Adverse events will be graded according to their significance for severe consequences, such as injury or death.

1. Examples of severe adverse events (life-threatening or disabling and requiring medical attention).  Severe adverse events that may occur during the CM intervention include death and cardiovascular events, though these are extremely rare in the absence of significant cardiac pathology. Other serious adverse events include suicidal ideation and/or self-injurious behaviors. For these adverse events, participants will be referred to the nearest emergency room.

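### The pooled CO-adherence threshold (14-17 of 25 visits) can be passed with no CO sample in weeks 14-24, so this row alone says nothing about monitoring in the monthly phase

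*Protocol*

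**What the plan says.** Table 1 (Administration and/or Delivery of Study Intervention) lists 25 incentive visits through week 24. The text of that section gives the same pattern, "daily for the first 7 days (week 1), twice weekly for the next 3 weeks (1 month), once weekly for the next 9 weeks (3", with visits at monthly intervals after that. The adherence row of Table 2 applies a single threshold to that total: "75% of those enrolled will provide a CO sample at 60%-70%, i.e., 14 -17 out of 25 possible assessment visits". It sets no minimum for any phase.

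Statistical Analysis Plans gives the reading rule: "Above-threshold findings will suggest a reasonable level of feasibility and acceptability for the corresponding aspects of study procedures". The sentence after it says that a result below threshold calls for changes to procedures or design before a full-scale trial.

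The Background says that recent work "has demonstrated the feasibility of short-term CM (8 weeks or less) for smoking cessation among homeless adults", and that no feasibility trial has yet looked at "extended CM, defined as CM for ≥12 weeks" in this population. Study Rationale sets the incentive period at 6 months.

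The weekly phase is not counted the same way throughout. Table 1, the visit text and the list of procedures for visits 15-23 give 9 weekly visits. The Schedule of Activities has "Visits 15-22/Weeks 5-13", which is 8, and the Data and Safety Monitoring Plan has "once weekly for the next 8 weeks (3 months").

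**The concern.** The pilot is meant to show whether CM carried on for 6 months can be run in this population. The distinctive late part of the schedule is a few monthly visits, and the protocol itself says that escalating payments matter because visits become less frequent. Yet the CO-adherence row gives every visit equal weight, so the early visits dominate the count. If participants attend well for three months and then give few or no monthly samples, the row can still come out above threshold and be read as support for the whole CO schedule. The full-scale trial would then inherit a monthly monitoring phase that this criterion had not tested.

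**Working it through.** **Inputs.** Visits per phase are 7, 6, 9 and 3 (Table 1). The threshold is 14-17 of 25, to be reached by 75% of those enrolled (Table 2). N = 90 (Sample Size), so the row passes when at least 0.75 x 90 = 67.5, that is 68, participants are adherent. The documents give no attendance rate by phase, so the rates below are assumptions. The one mean rate they cite is 60% of visits with a CO reading, from a prior study.

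**The plan's own figure.** 7 + 6 + 9 + 3 = 25 reproduces the total. 60% of 25 is 15.0 and 70% of 25 is 17.5. The upper end (17) agrees after rounding down. The lower end does not: 14/25 = 56%, not 60%.

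**Cumulative visits.** Week 1: 7. Week 4: 13. Week 5: 14. Week 8: 17. Week 13: 22. Week 24: 25. So 22/25 = 88% of visits fall by week 13 and 3/25 = 12% after it. With perfect attendance, 14 is reached in week 5 and 17 in week 8. These are the earliest possible dates.

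**Attendance needed with nothing after week 13.** 14/22 = 64% and 17/22 = 77%.

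**Chance that the row passes with no visit after week 13.** Assume independent visits with constant attendance probability p through week 13. The chance that one person is adherent is q = P(Bin(22, p) ≥ k), and the chance that the row passes is P(Bin(90, q) ≥ 68).

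| p | q, k = 14 | row passes, k = 14 | q, k = 17 | row passes, k = 17 |
| --- | --- | --- | --- | --- |
| 0.60 | 0.454 | about 0 | 0.072 | about 0 |
| 0.65 | 0.647 | 0.02 | 0.163 | about 0 |
| 0.70 | 0.814 | 0.94 | 0.313 | about 0 |
| 0.75 | 0.925 | >0.99 | 0.517 | about 0 |
| 0.80 | 0.980 | >0.99 | 0.733 | 0.36 |
| 0.85 | 0.997 | >0.99 | 0.900 | >0.99 |

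**Sensitivity to variation between people.** Let p follow a beta distribution with a + b = 8 (assumed). At a mean of 0.70 the cut of 14 passes with probability 0.16 instead of 0.94. At a mean of 0.80 the cut of 17 passes with 0.07 instead of 0.36, and at a mean of 0.85 with 0.84.

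**Sensitivity to the weekly count.** With 8 weekly visits there are 7 + 6 + 8 = 21 visits by week 13. The cut of 14 then passes with 0.29 at p = 0.70 and >0.99 at 0.75; the cut of 17 with 0.001 at 0.80 and 0.89 at 0.85. The week 5 and week 8 crossing points do not move.

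**Other rows of Table 2.** Retention is required at 6 months (75%) and 1 year (75%), and 75% must complete all questionnaires, which include those at 6 months and 1 year. The counseling row concerns 12 sessions. None asks for a CO sample at the monthly visits between month 3 and month 6.

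**The case against.** The strongest reply is that Table 2 is read row by row and one sub-threshold row is enough to call for remedial changes. If attendance stopped after week 13, the 6-month and 1-year retention rows and the all-questionnaires row would be expected to fail. The 6-month assessment is ordinarily one of the three late visits and includes CO, with urine for those who report abstinence and have low CO. Telephone check-in is described only between 6 and 12 months. CO-negative samples, visits attended and 6-month verified abstinence are also endpoints, so a late decline would be visible in the data.

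Most of this stands. A reader might infer that the pilot could send a 24-week design forward on short-term evidence only; the documents do not support that, because the other rows reach past week 13. What remains is narrower. Retained is not defined as having given a CO sample, the related endpoints are pooled totals without thresholds, and no row covers the intermediate monthly samples.

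Two further inferences also fail. The threshold is not simply met by weeks 5-8: with 60% attendance the chance that one person has 14 visits by week 8 is 5%, and with 70% it is 20%. Nor do weeks 14-24 define extended CM, which the protocol puts at 12 weeks or more. Counted from the end of the 8 weeks already shown feasible, weeks 9-24 hold 5 + 3 = 8 of 25 visits (32%).

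Finally, at the cited 60% mean attendance the row would fail at either cut if nobody came after week 13. The weakness shows only when early attendance is clearly better than that.

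**Conclusion.** The point holds for this row, not for the pilot as a whole. The CO-adherence threshold can be passed without any sample in weeks 14-24, so passing it is no evidence that CO monitoring works in the monthly phase of the 6-month schedule. That follows from the visit counts alone. A full late collapse should show up in other rows; the unguarded part is mainly the monthly CO visits before the 6-month assessment.

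How likely a misleading pass is depends on assumed early attendance and on which end of the 14-17 range is used. With nobody attending after week 13 and independent visits, the change from near-certain fail to near-certain pass lies between 65% and 75% early attendance for the cut of 14, and between 75% and 85% for the cut of 17. Variation between people or an 8-visit weekly phase lowers the probabilities in the transition range. This is a worthwhile, inexpensive improvement to one progression criterion. It does not invalidate the design.

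**What to change.** Keep the overall count. Report CO-sample adherence separately for weeks 1-4, 5-13 and 14-24. Add to Table 2 a threshold for weeks 14-24, at a level the sponsor chooses, and read it on its own under the rule in Statistical Analysis Plans. For example, a stated share of those enrolled could be required to give a sample at 2 of the 3 visits; that figure is only an illustration and has no source in the documents.

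In the same edit, replace the 14-17 range with one cut, correct the mismatch between 14 visits and 60%, and reconcile the 8 and 9 weekly visits so that the denominator is settled.

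The cost is one line in Table 2 and a tabulation of data already collected at each visit. The downside is one more criterion that can fall below threshold, and a coarse score, since each person has only 3 visits in that phase.

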**Intervention.** In addition to receiving usual cessation care, CM intervention participants with CO-verified abstinence will obtain a CM incentive payment, via gift cards redeemable in national retail chains, according to a pre-defined schedule. Gift card amounts and assessment frequencies are based on prior studies among individuals experiencing homelessness or with substance use disorders,^26,30,32,33,38^ and are expected to be effective in promoting smoking cessation. We think this CM schedule is close to what will be adopted; however, our results from Aim 1 will inform the protocol. Gift card amounts will begin at US $13 and increase by $0.50 for each negative CO specimen throughout the first 6 months of the program to a maximum of $24.50 per specimen for a total of 25 specimens collected through week 24 (Table 3). An escalating schedule that increases per visit incentive payment over time is especially important in this study to maintain motivation as visit frequency decreases over time. The total amount that participants can earn under the contingent incentive program through week 24 is $620, an amount comparable to what has been used in prior studies.^30-33^ Test results indicative of smoking (i.e. CO >5ppm) or missed visits will lead to resetting the gift card amount back to the initial low value, but two consecutive negative tests will restore the value back to the highest level previously achieved. ^26,30,32,33,100^

**Control condition.** Control group participants will receive a fixed amount of $5 for attending each abstinence assessment visit and participate in usual cessation care, as described above.^32^ This approach has been used in a prior study of CM for smoking cessation among homeless adults.^32^

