Our threshold estimates for outcomes are based on findings from prior studies. For example, for the outcome of adherence to the CO assessment visits, a prior study showed that 78% of participants attended half of the assessment visits. Another study showed that participants provided a CO reading on average for 60% of the total possible assessment visits.^32,33^ We will assess the following process outcomes: number of counseling sessions attended (verified through the EHR), prescribed NRT (verified through the EHR), use of NRT and number of days used (determined by self-report at each assessment visit), total number of follow-up visits, number and amount of incentives received, and the incentive cost per quit attempt (i.e., the cost of incentives for a participant who achieves abstinence at each time point compared to a participant who does not). We will explore perceptions around CM payment amounts and perceived efficacy of the payment amounts in motivating long-term abstinence. We will conduct this evaluation using a combination of methods including notes/memos from staff during the study and in-depth interviews with clinic staff and patients at the TWUHC, RFPC, and PHP around satisfaction with the clinical trial. We will invite patient (n=15) and staff (n=8) participants to participate in a closing interview about the study.

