#### Visits 15-23 (Week 5-13)

- Review of concomitant medications
- Adverse Events assessment
- Administration of Study Intervention: Contingent incentives for smoking cessation
- Protocol-specific assessments/procedures: Expired carbon monoxide sample and a brief questionnaire weekly; Questionnaires at 3 months follow-up;

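### The CO-adherence threshold equates 60%-70% of 25 visits with 14-17 samples, gives a range instead of one cut-off, and rests on an inconsistent visit count

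*Protocol*

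**What the plan says.** Table 2 of the protocol, under Adherence Assessment, lists the feasibility and acceptability thresholds. For the CO assessment schedule it requires "75% of those enrolled will provide a CO sample at 60%-70%, i.e., 14 -17 out of 25 possible assessment visits". The two other thresholds in the same cell are written as minimums: at least 6 of 12 counseling sessions, and NRT use for at least half of the treatment duration.

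The text below the table says the thresholds come from prior studies and gives two examples for this one: "a prior study showed that 78% of participants attended half of the assessment visits", and, from another study, CO readings at an average of 60% of possible visits.

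Under Statistical Analysis Plans, the primary analysis compares each indicator descriptively with its tabled threshold. A result below threshold points to changes in procedures or design before a full-scale trial.

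On the number of CO visits, the section on administration and delivery of the intervention speaks of incentives "for a total of 25 specimens collected through week 24" and of visits "once weekly for the next 9 weeks (3 months"). Table 1 there also shows nine weekly visits and a total of 25. The visit headings under Study Procedures agree: "Visits 15-23 (Week 5-13"). The Schedule of Activities has "Visits 15-22/Weeks 5-13" followed by "Visits 23-25/Weeks 16-24", and Appendix 1, section 2, has "once weekly for the next 8 weeks (3 months").

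**The concern.** The CO threshold is one of the pilot's criteria for whether the outcome schedule can be followed. It can be applied only if it names one number of samples, out of one number of visits, that a participant must reach. As written, the percentage and the count disagree, neither is marked as a minimum, and the denominator differs between parts of the protocol. Someone would have to choose the cut-off later, possibly with the data in view, and that choice could decide whether the criterion is met.

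This is not detail that a protocol normally leaves to a statistical analysis plan. The protocol fixes the figure itself, and fixes it in a form that contradicts itself.

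**Working it through.** **1. The stated counts.** Inputs from Table 2: 60%-70%, 14-17 samples, 25 visits. Formula: share × visits.

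| Visits | 60% | 70% | Smallest count reaching 60% | Smallest count reaching 70% | 14 as a share | 17 as a share |
| --- | --- | --- | --- | --- | --- | --- |
| 25 | 15.0 | 17.5 | 15 | 18 | 56% | 68% |
| 24 | 14.4 | 16.8 | 15 | 17 | 58.3% | 70.8% |

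On 25 visits the plan's 14-17 does not reproduce. Because 0.60 × 25 is exactly 15, no rounding rule gives 14. The upper figure of 17 can be defended as 17.5 rounded down. On 24 visits, rounding to the nearest whole number gives 14 and 17.

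**2. The range.** Four cut-offs can be read from the line on 25 visits: 14 (lower count), 15 (lower percentage), 17 (upper count) and 18 (upper percentage, rounded up). The required share is 0.75 × 90 = 67.5, so 68 of 90 participants. If at least 68 reach 14 samples but fewer than 68 reach 17, the criterion is met at one end of the stated counts and missed at the other. Read literally, the range would even leave out participants who give more than 17 samples, which cannot be intended.

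**3. The visit count through week 24.**
- Table 1 and main text: 7 + 6 + 9 + 3 = 25.
- Visit headings under Study Procedures (2-8, 9-14, 15-23, 24-26): 7 + 6 + 9 + 3 = 25.
- Schedule of Activities (2-8, 9-14, 15-22, 23-25): 7 + 6 + 8 + 3 = 24.
- Appendix 1: 7 daily, 3 × 2 = 6 twice-weekly and 8 weekly visits; with the three monthly visits of Table 1 this is 7 + 6 + 8 + 3 = 24.

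At the 60% end the denominator does not matter, since 15 is the smallest qualifying count on either schedule. At the 70% end it moves the cut-off from 17 to 18.

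**4. The cited prior figures.** The threshold is a share of participants (75%) reaching 60%-70% of visits. The first cited figure is a share of participants (78%) at half of the visits. The second is a mean over participants (60%). Neither is on the threshold's scale.

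The mean constrains the threshold very little. If exactly 75% of participants give 15 or more of 25 samples, mean attendance can lie anywhere from 0.75 × 15/25 = 45% to 0.75 + 0.25 × 14/25 = 89%. A mean of 60% is inside that interval.

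**The case against.** The strongest defence is that this is a one-visit slip and a loosely worded target in a descriptive pilot. The plan proposes no inferential statistics, the line is one of three adherence thresholds within a longer table, and missing it only suggests changes. All of that stands, and it limits the severity. It does not make the line usable, because a comparison with a tabled threshold still needs one threshold.

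The visit-count conflict can also be read as numbering. The Schedule of Activities passes from visit 25 to visit 27 with no visit 26, while the visit headings run 15-23, 24-26 and 27. That makes a slip in the table plausible. It does not account for the eight weeks in Appendix 1, and the protocol does not say which version governs. A reader might conclude that 14-17 was calculated on a 24-visit schedule. The counts fit, but nothing in the protocol says so, and Table 2 itself names 25.

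A reader might also infer that the threshold exceeds the prior results it is said to rest on, so that a pilot matching those results would fail on every reading. The documents do not support this. Suppose 75% of participants give 18 samples, 3% give 13 and 22% give 5. Mean attendance is (0.75 × 18 + 0.03 × 13 + 0.22 × 5)/25 = 14.99/25 = 59.96%, and 78% reach 13 or more, which is at least half of 25. Both cited figures are matched, and 75% pass at 14, 15, 17 and 18. A smooth shape, a beta-binomial with the same mean of 60% and 78% at 13 or more, puts only 57% at 15 or more. The cited figures allow either outcome. They also come from two separate studies and are offered only as examples.

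**Conclusion.** The point holds in three parts.

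- The stated count is wrong at the lower end by one visit: 14 of 25 is 56%, not 60%.
- The threshold is a span from 14 to 17 samples (12 percentage points of visits) with no pass mark, so its result can depend on which end is used.
- The number of CO visits through week 24 is 25 in some places and 24 in others.

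These rest on the protocol's own figures. The only added assumption is that Appendix 1 shares the three monthly visits of Table 1.

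The two prior-study figures do not by themselves yield 75% of participants at 60%-70% of visits. Whether the threshold is stricter or looser than those results cannot be determined without the distribution of attendance, which the protocol does not give. There is therefore no basis here for asking that the 75% or the visit mark be lowered; a target may be set above earlier performance on purpose.

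This should be fixed before the criterion is applied. It does not bear on any effect estimate.

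**What to change.** - In Table 2, replace the range with one whole-number minimum and its denominator, for example at least 15 of 25 CO samples. Fifteen is at least 60% of either 24 or 25 visits (62.5% and 60%), so this number survives whichever count is confirmed. If the sponsor intends another point in the range, it should state that number and make the percentage agree with it.
- Reconcile the number of weekly visits and the visit numbering across Table 1, the Schedule of Activities, the visit headings under Study Procedures, and Appendix 1, section 2. Which version is right is for the sponsor to say.
- Add one sentence on how 75% of participants at the chosen mark was arrived at, or say that it is a target informed by the cited studies but not derived from them.

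The cost is a few words in Table 2 and in the text below it, plus whichever visit-count entries prove to be wrong. Sample size and data collection need not change. The cut-off should be fixed before adherence data are summarised.
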